#### The Exercise Adherence Rating Scale - EARS

EARS is a patient-reported outcome measure composed of six items that directly assess adherence behavior. In the present study, it will be used to assess the perception of adherence to prescribed home exercises. It was translated and validated into Brazilian Portuguese [38]. The six items should be summed and items with positive phrases are reversely scored, meaning items 1, 4, and 6. The six items are scored using an ordinal Likert scale of possible answers (0 = strongly agree to 4 = totally disagree), with higher scores indicating greater adherence (0 to 24). Participants will answer the EARS only at the end of the treatment, to assess retrospectively the adherence behavior.

### Interventions—general procedure

On both groups, participants will be submitted to craniofacial manual therapy and an exercise program comprised of Orofacial Exercises and Neck Motor Control Exercises. The participants will be submitted to a program of six weeks of craniofacial manual therapy, orofacial exercises, and neck motor control exercises. The program will be carried out twice a week, one session in the outpatient clinic and another day in the week, the participants will be invited to perform home-based exercises.

Each session will last one hour, always conducted by the same physiotherapist. The first three sessions, participants will be submitted to orofacial manual therapy techniques (myofascial release) and neck motor control exercises (Table 2). And in the remaining sessions, participants will perform half the session orofacial exercises and the other half, neck motor control exercises (Table 2). In the first three weeks, only neck motor control exercises (cervical bracing in different positions) will be home-based prescribed. In the last 3 weeks, participants will be instructed to perform orofacial exercises and neck motor control exercises (Table 2).

**Table 2 Tab2:** The schedule of the interventions administered in the study. The cervical motor control exercises will be administered according to the progression of the patient in each level

		Orofacial manual therapy and exercises	Neck motor control exercises	Pain education
**Week 1**	Outpatient clinic	Myofascial release (Fig. 2)	Cervical bracing (Fig. 4) Neck dynamic isometric exercises (Fig. 5) Neck functional exercises (Fig. 6)	Pain neuroscience education^a^
	Home exercises		Cervical bracing (Fig. 4)	
**Week 2**	Outpatient clinic	Myofascial release (Fig. 2)	Cervical bracing (Fig. 4) Neck dynamic isometric exercises (Fig. 5) Neck functional exercises (Fig. 6)	Pain neuroscience education^a^
	Home exercises		Cervical bracing (Fig. 4)	
**Week 3**	Outpatient clinic	Myofascial release (Fig. 2)	Cervical bracing (Fig. 4) Neck dynamic isometric exercises (Fig. 5) Neck functional exercises (Fig. 6)	
	Home exercises		Cervical bracing (Fig. 4)	
**Week 4**	Outpatient clinic	Mandibular exercises (Fig. 3)	Cervical bracing (Fig. 4) Neck dynamic isometric exercises (Fig. 5) Neck functional exercises (Fig. 6)	
	Home exercises	Mandibular exercises (Fig. 3)	Cervical bracing (Fig. 4)	
**Week 5**	Outpatient clinic	Mandibular exercises (Fig. 3)	Cervical bracing (Fig. 4) Neck dynamic isometric exercises (Fig. 5) Neck functional exercises (Fig. 6)	
	Home exercises	Mandibular exercises (Fig. 3)	Cervical bracing (Fig. 4)	
**Week 6**	Outpatient clinic	Mandibular exercises (Fig. 3)	Cervical bracing (Fig. 4) Neck dynamic isometric exercises (Fig. 5) Neck functional exercises (Fig. 6)	
	Home exercises	Mandibular exercises (Fig. 3)	Cervical bracing (Fig. 4)	

^a^Pain education was administered just for one group

Pain neuroscience education will be administered only to one group in the first and second sessions (half of the session). To balance the clinical attention offered to patients in both groups, the group not submitted to PNE will be invited to clarify possible doubts regarding the home exercises.

#### The Orofacial Exercises and Orofacial Manual Therapy

The protocol of Orofacial Exercises and Manual Therapy reported by Kalamir et al. [39] will be adopted in the present study. The manual therapy techniques: intraoral temporalis muscle release, intraoral medial and lateral pterygoid (origin) muscles technique, and intraoral sphenopalatine ganglion technique (Fig. 2). And two mandibular exercises: Mandibular body—condylar cross-pressure chewing technique and post-isometric relaxation stretches in jaw laterotrusion and jaw opening (Fig. 3). Each exercise will be executed 10 times per session for 10 s. Participants gave written consent for use of his/her images on pictures 2 to 6.

**Fig. 2 Fig2:**
[figure not shown]
The manual therapy techniques. **A** Intraoral temporalis myofascial release: The therapist will be positioned by the side in which the technique will be administered, one hand will be on the coronoid process of the mandible with pressure according to the patient's tolerance, while the other hand will be along the temporal muscle. The patient will perform opening movements of the mouth gradually until the maximum opening. **B** Intraoral medial and lateral pterygoid (origin) technique: The therapist will be positioned contralateral by the side in which the technique will be administered, and with the index finger, the therapist will press the origins of the pterygoid muscles, the pressure will be carefully maintained for 5 s. **C** Intraoral sphenopalatine ganglion technique: The therapist's index finger will be slowly inserted along the buccal surface of the slightly occluded teeth, the patient will tighten the teeth and, after relaxing, the therapist will apply pressure behind the lingual surface of the masseter and medial pterygoid, this process is repeated until the fingertip approaches the anterior surface of the infratemporal fossa/sphenopalatine fossa, in a comfortable way for the patient

**Fig. 3 Fig3:**
[figure not shown]
Mandibular exercises. (**A**) Mandibular body - condylar cross-pressure chewing technique. Post-isometric relaxation stretches – jaw laterotrusion (**B**) and jaw-opening (**C**). Arrows indicate the direction of the movements. * Direction of the movement of the hand

#### Neck motor control exercises

The neck motor control protocol reported by Celenay et al. [40] will be adopted in our study. The exercise program has three levels: (1) *cervical bracing*, (2) *neck dynamic isometric exercises*, and (3) *neck functional exercises*.

The *cervical bracing exercises* include four hierarchical levels in neurodevelopment stages (supine, prone, quadrupedal, bipedal) for the cervical spine (Fig. 4). The intermediate level exercises will be comprised of upper and lower extremity range of motion exercises while maintaining a stable spine in four-, three-, or two-point kneeling (Fig. 4C–E). The high-level exercise will be the cervical bracing in the upright position (Fig. 4F).

**Fig. 4 Fig4:**
[figure not shown]
Neck motor control exercises program. **A**–**C** Cervical bracing on neurodevelopment stage positions. **D**, **E** The cervical bracing with extremity range-of-motion movements. **F** Cervical bracing in the standing position—movement against the wall. Arrows indicate the direction of the movements. * Direction of the movement against the wall

The *neck dynamic isometric exercises* (five hierarchical levels) will be carried out directly forward, obliquely, toward right and left, and directly backward by maintaining a stable spine with elastic resistive bands (Fig. 5).

**Fig. 5 Fig5:**
[figure not shown]
Neck motor control exercises program—neck dynamic isometric exercises were performed directly forward (**A**), obliquely, toward right (**C**) and left (**B**), and directly backward by maintaining a stable spine with elastic resistive bands (**D**, **E**). Arrows indicate the direction of the movements

Finally, *neck functional exercises* will include functional training with elastic resistance and exercise balls on unstable surfaces (eight hierarchical levels) (Fig. 6A–H). The criteria to progress in each level (cervical bracing, neck dynamic isometric exercises, and neck functional exercises) will be holding the contraction, for 10 s, 10 times. The progression of the exercises adopted will follow the sequence described on Figs. 4, 5, and 6.

**Fig. 6 Fig6:**
[figure not shown]
Neck motor control exercises program—functional training on unstable surface was performed in combination with cervical bracing over the ball (**A**–**C**), with ball in standing position (**D**–**F**) and with ball and elastic resistance (**G**, **H**). Arrows indicate the direction of the movements. * Direction of the movement against the wall

Participants will be oriented to contract deep neck flexor muscles only during the exercises, not throughout the day as described in the protocol of the original paper [40].

#### Pain neuroscience education (PNE)

All participants in the G1 will initially receive two additional sessions in which a workshop on PNE will be administered and discussed. A power-point presentation with metaphors and animated videos will be employed. The PNE program will be held in 2 sessions of 40 min each. The intervention program will be divided into 17 thematic topics according to explain pain [41]:
Contextualization on the importance of the program: how pain causes suffering and its alarming increase in the worldInitial concepts on neurosciences and painHow context can influence pain perception—incredible stories on painHuman beings as a multisensory complex—sensory information is reaching the brain all the timePain output may be deflagrated by memory, not only nociceptionNociception and the concept of pain as a response of protection/the nociceptorsThe incorrect concepts on pain (pain system, pain receptors, pain area in the brain)Concepts on pain neurophysiology—synapses, spinal horn, primary and secondary order neuronsTypes of sensitization/descending nociception modulation systemThe danger message and the brain processingThe sensitized brain and its relationship to chronic painThe contribution of other systems to pain experience and vice-versa: endocrine, parasympathetic/sympathetic, immune, and motorHow bone, muscles, and nerves send sensory information all the timeFear-avoidance model revisitedEncouragement to changeHow to develop positive attitudesConcepts of graded exposure and graded activity - (at least two questions). We will reconceptualize the beliefs of the questions with higher scores on TSK/TMD. A schedule will be developed together with the patient to favor patient exposition to activities they used to avoid.

### Sample size calculation

The study was designed to detect a between-group difference of 2 points in pain intensity (30%) measured by the NPRS, with an estimated standard deviation of 3 points. A previous study [42] recommended a minimum sample size of n=61 per group.

For disability, a between-group difference of 5.08 points for disability measured by the CF-PDI, considering the Smallest Detectable Change of CF-PDI Brazilian version [26], with an estimated standard deviation of 10 points resulted in a sample size of 64 participants per group. The other specifications were power of 80%, an alpha of 5%, *f* test of 0.33 (pain intensity) and 0.25 (disability). Therefore, a total of 128 participants was obtained, however considering a follow-up loss up to 15%, we will recruit 148 participants. G*Power was used to run the sample size calculation (GPower 3.0.10, da University of Kiel, Germany).

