## Methods

### Trial design

This study will be a randomized clinical trial with two parallel arms, following the recommendations of the Consolidated Standards of Reporting Trials - CONSORT [20].

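### Recruiting 148 covers a follow-up loss of 13.5%, not the stated 15%, on the required 128; the effect on power is negligible

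*Protocol article*

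**What the plan says.** The trial is described as a "randomized clinical trial with two parallel arms". All the figures at issue stand in the Protocol article, section Sample size calculation.

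- **Disability.** It sets the total. The plan assumes "a between-group difference of 5.08 points for disability measured by the CF-PDI", "with an estimated standard deviation of 10 points", which "resulted in a sample size of 64 participants per group".
- **Pain intensity.** A minimum of 61 per group is given, so this outcome does not drive the total.
- **Other settings.** Power is 80%, alpha is 5%, and the effect size f for disability is 0.25.
- **Total and allowance.** From these, "a total of 128 participants was obtained", and then, "considering a follow-up loss up to 15%, we will recruit 148 participants".

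The abstract and the section Eligibility criteria and participants repeat 148. The inflation formula is not shown. The sections Analysis of the population and Data analysis both state an intention-to-treat analysis in which missing values are filled with the last available assessment.

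**The concern.** An allowance for loss is meant to leave the required number in follow-up after the stated proportion of recruits has gone. Because the loss is a proportion of those recruited, the required number has to be divided by one minus the loss. The stated 148 is smaller than that calculation gives.

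At stake is the accuracy of a design statement. A trial that lost 14% to 15% would be reported as within its planned tolerance although fewer than 128 participants had observed follow-up.

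**Working it through.** **Inputs** (all from Sample size calculation): 128 required, 64 per group; loss up to 15%; 148 to be recruited; disability difference 5.08, SD 10; f = 0.25; power 80%; alpha 5%. Sidedness is not stated. I take the test as two-sided, which an F test implies.

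**1. The plan's base number.** For two equal groups d = 2f, so f = 0.25 gives d = 0.50. A two-sample t test at two-sided 5% and 80% power needs 63.8 per group, so 64 per group and 128 in total. The plan's figure is reproduced.

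**2. The plan's 148.**
- Whole trial: 128 x 1.15 = 147.2, rounded up to 148.
- Per arm: 64 x 1.15 = 73.6, rounded up to 74, and 2 x 74 = 148.

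Both routes give the stated figure.

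**3. What 148 leaves at 15% loss.**
- 148 x 0.85 = 125.8.
- In whole participants, 15% of 148 is 22.2, so at most 22 can be lost within the ceiling: 148 - 22 = 126, or 63 per group if the arms are equal.
- Shortfall against 128: 2 participants.

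**4. What 15% would need.**
- Whole trial: 128/0.85 = 150.6, so 151.
- Equal arms: 64/0.85 = 75.3, so 76 per arm and 152 in total.
- This is 3 to 4 more than 148.

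**5. The loss that 148 does cover.** (148 - 128)/148 = 20/148 = 13.5%.

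**6. Power for disability** (two-sample t test, two-sided 5%). The unrounded effect is d = 5.08/10 = 0.508, that is f = 0.254.

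| Per group | d = 0.50 (rounded f = 0.25) | d = 0.508 (5.08 with SD 10) |
|---|---|---|
| 64 | 80.1% | 81.4% |
| 63 | 79.5% | 80.8% |
| 62 | 78.9% | 80.1% |

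Going from 64 to 63 per group costs about 0.6 percentage points. With the unrounded effect, 61.8 per group, so 62, already gives 80%.

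**7. Pain intensity.** 63 per group still exceeds the 61 that the plan states for this outcome.

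**The case against.** Several points can be made for leaving the text alone.

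- **Everyone is analysed anyway.** With intention to treat and carried-forward values, all randomised participants enter the main analysis, so a 15% loss does not shrink it to 126. This stands. The 126 counts participants with observed follow-up, not the size of the main analysis. But the article itself sets an allowance to protect 128 against loss, and by that reasoning 148 falls short. Losses during treatment would also directly reduce the per-protocol analysis, which drops those who do not complete the six weeks.
- **15% is a ceiling.** This also stands. The article does not forecast 15%, so 126 should not be called the expected number. A ceiling of 15% still includes 15%, and 148 falls short for any loss above 13.5%.
- **Power is not harmed.** This is correct on the stated 5.08 and SD 10. The 79.5% arises only because f was rounded from 0.254 to 0.25.
- **Arm sizes will vary more than this.** Under the simple randomisation described in Procedures, randomization, and allocation, the SD of one arm's size is the square root of 148 x 0.5 x 0.5, about 6. That outweighs a gap of one participant per arm. It bears on the importance of the point, not on the arithmetic.

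A reader might infer that the trial is underpowered, or that the authors demonstrably multiplied by 1.15. The documents support neither. Power stays at about 80% on either effect size, and the multiplication is only a likely explanation drawn from an exact numerical match.

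**Conclusion.** The statement is wrong as printed, and the point is minor. The figures 128, 15% and 148 cannot all hold: 148 covers a 13.5% loss of observed follow-up, and at the 15% ceiling about 126 participants would remain, 2 below the target. The finding follows from the article's own numbers and does not depend on how 148 was reached.

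The effect on power is negligible: 80.8% for the stated disability difference and SD, or 79.5% at the rounded f. These power figures assume a two-sided t test, equal arms and observed data only. No conclusion about the adequacy of the trial follows from this.

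**What to change.** Either of two wordings in Sample size calculation resolves it.

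1. Keep 148 and state that it allows for a 13.5% loss of observed follow-up (20 of 148).
2. Keep 15% as the ceiling and add that, at that loss, about 126 participants would have observed follow-up. Give disability power there as 80.8% for a difference of 5.08 with SD 10, noting 79.5% at f = 0.25.

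The first is simpler. With the second, both power values should appear, since 79.5% alone would reflect a rounded effect size. The cost is one edited sentence: no additional patients, and no change to design or analysis.

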### Data analysis

The mean effects of the interventions and the group differences for all outcomes (primary and secondary) will be calculated using linear mixed models, incorporating terms for the treatment groups, time (post-intervention and follow-up), and interaction terms (treatment subgroups and time) as well as, psychosocial variables, knowledge about pain neurophysiology (score on the NPQ), sex, ethnicity, and age as covariates. Secondary analysis will be conducted using regression models to determine whether baseline scores of psychosocial variables (HADS, PCS, TSK/TMD) will moderate the effect of treatments. All data will be double entered prior to the analysis. The analysis will follow the intention-to-treat principles. Additionally, we will adopt analysis per protocol excluding patients that did not complete the 6 weeks of treatment. The statistician will receive coded data and will be blinded to the participants’ allocation groups. The data collected will be stored coded to protect patient confidentiality. In order do to handle missing data, we will replace the value by the last observation carried forward. For all analysis, we will use the IBM SPSS software package, version 22 (IBM Corp, Armonk, NY) and the significance level will be established at 0.05.

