### Procedures, randomization, and allocation

Once the patient has accepted the invitation to participate and signed the formal consent to participate, one researcher will run the assessment to determine eligibility. After this initial assessment, participants will be randomly assigned following simple computerized randomisation procedures to one of the two treatment groups through the use of cards previously placed in opaque sealed envelopes: G1 – Pain Neuroscience Education + craniocervical manual therapy and exercises or G2 - craniocervical manual therapy and exercises. The allocation sequence will be generated by a researcher not involved in the assessment and interventions ([name]), and another research assistant will assign participants to interventions (Fig. 1). Figure 1 shows the trial procedure, and Table 1 illustrates the trial schedule.

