**Table 1 Tab1:**
[figure not shown]
Recommended protocol items: schedule for enrollment, interventions, and assessments

*PNE* = pain neuroscience education, *HADS* = Hospital Anxiety and Depression Scale, *PCS* = Pain Catastrophizing Scale, *CF-PDI* = Cranio Facial Pain and Disability Inventory, *PSEQ*= Pain Self-Efficacy Scale, *TSK/TMD* = Tampa Scale for Kinesiophobia for Temporomandibular Disordes, *NPQ =* Neurophysiology of Pain Questionnaire, *GPE* = Global Perceived Effect, *EARS* = The Exercise Adherence Rating Scale

One blinded researcher regarding treatment group allocation will run the assessments pre-treatment, immediately after and at 1-month and 3-month follow-ups. The evaluations of the study will be carried out according to the recommendations of the Initiative on Methods, Measurement and Pain Assessment in Clinical Trials (IMMPACT) for chronic pain [24].

During the assessment for eligibility, the participants will be assessed according to RDC/TMD to confirm the presence of TMD [21]. Afterwards, the participants will answer the Pain Numeric Rating Scale (NPRS) [25], The Craniofacial Pain and Disability Inventory (CF-PDI) [26], Global Perceived Effect (GPE) of improvement [25], Tampa Scale for Kinesiophobia for Temporomandibular Disorders (TSK/TMD )[27], Pain Catastrophizing Scale (PCS) [28], Pain Self-Efficacy Questionnaire (PSEQ) [29], Revised Neurophysiology of Pain Questionnaire (NPQ) [30], and Hospital Anxiety and Depression Scale (HADS) [31]. This protocol followed the Standard Protocol Items: Recommendations for Interventional Trials (SPIRIT) recommendations [32].

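### The stated mixed model leaves out the baseline values of the two primary outcomes (NPRS and CF-PDI); this gives up precision but does not threaten validity or the planned power

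*Protocol article*

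**What the plan says.** The Data analysis section names the terms of the model. They are treatment group, time and their interaction, with time spelled out: "incorporating terms for the treatment groups, time (post-intervention and follow-up), and interaction terms (treatment subgroups and time"). The covariates are "psychosocial variables, knowledge about pain neurophysiology (score on the NPQ), sex, ethnicity, and age as covariates". Two sentences on, the moderation analysis shows what is meant by psychosocial variables: "baseline scores of psychosocial variables (HADS, PCS, TSK/TMD) will moderate the effect of treatments". Neither primary outcome is among them.

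The baseline values exist. The text after Table 1 says that a blinded assessor "will run the assessments pre-treatment, immediately after and at 1-month and 3-month follow-ups", and the list of instruments at the initial assessment opens with pain intensity ("Afterwards, the participants will answer the Pain Numeric Rating Scale (NPRS") and continues with CF-PDI. Under Procedures, randomization, and allocation, "participants will be randomly assigned following simple computerized randomisation procedures"; no stratification or minimisation on baseline severity is stated.

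**The concern.** In a pain trial the score before treatment is usually among the strongest predictors of the score after it. The listed model adjusts for demographic and psychological characteristics but not for this one. As written, the treatment effect on NPRS or CF-PDI is a comparison of post-treatment means that takes no account of where each participant started. Variation that baseline could explain stays in the residual, so intervals are wider than they need be. Because allocation is simple, any chance difference in baseline severity also passes, in proportion to the baseline-outcome correlation, into this trial's estimate. These are two views of one cost: the standard error of the unadjusted comparison already includes the play of chance at baseline.

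**Working it through.** **Inputs from the Sample size calculation section.** CF-PDI: difference 5.08, SD 10, f = 0.25, 64 per group. NPRS: difference 2, SD 3. Power 80%, alpha 5% (sidedness is not stated; two-sided is used here). The total of 128 is raised to 148 for losses.

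**Assumption.** The documents give no correlation r between baseline and follow-up scores. A range of 0.3 to 0.7 is used.

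**Step 1: reproduce the plan's figure.** With two groups d = 2f = 0.50. The two-sample t calculation at d = 0.50 and 80% power gives 63.8, so 64 per group, as stated. Power at 64 is 80.1%. (With d = 5.08/10 = 0.508 it is 81%.) The calculation contains no baseline adjustment, so the planned power does not depend on one.

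**Step 2: CF-PDI with the baseline score as covariate, at a single visit.** Residual SD = SD × √(1 − r²), so the effective d is 0.50/√(1 − r²). The standard error is 10 × √(1 − r²) × √(2/64).

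| r | variance factor 1 − r² | SE factor | SE (points) | effective d | power, 64 per arm |
|---|---|---|---|---|---|
| none | 1 | 1 | 1.77 | 0.500 | 80% |
| 0.3 | 0.91 | 0.95 | 1.69 | 0.524 | 84% |
| 0.5 | 0.75 | 0.87 | 1.53 | 0.577 | 90% |
| 0.7 | 0.51 | 0.71 | 1.26 | 0.700 | 98% |

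The first row has no covariates at all. The planned model has several, and to the extent that they correlate with baseline disability they already recover part of the gain. The power figures in the lower rows are therefore upper limits on what adding baseline would achieve.

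**Step 3: NPRS.** d = 2/3 = 0.67, and power at 64 per arm without adjustment is about 96%. Little power remains to be gained. The standard error, 3 × √(2/64) = 0.53 points, would fall to 0.51, 0.46 or 0.38 at r = 0.3, 0.5 or 0.7. The 95% half-width (1.96 × SE) would go from 1.04 points to 0.99, 0.90 or 0.74.

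**Step 4: the same cost seen as chance imbalance (CF-PDI, baseline SD taken as 10).** At 64 per arm the baseline difference between groups has SD 10 × √(2/64) = 1.77 points. An unlucky difference of 1.96 × 1.77 = 3.5 points would shift the unadjusted effect by r × 3.5, that is about 1.0, 1.7 or 2.4 points, against a target of 5.08. This is the edge of the 95% range, not an expected shift, and it does not add to the loss in step 2.

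**Step 5: is change from baseline an equal substitute?** Its SD is 10 × √(2(1 − r)). With d = 0.50 and 64 per arm, power is 66% at r = 0.3 (below the unadjusted 80%), 80% at r = 0.5 and 95% at r = 0.7. At each of these values it falls short of the covariate adjustment in step 2.

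**The case against.** The strongest reply is that the reading hangs on one loosely worded parenthesis in a condensed article. The same sentence speaks of treatment subgroups in a two-group trial. The section also promises mean effects of the interventions as well as group differences, and a within-group effect normally needs a starting value. It carries the last observation forward, which for someone lost before the first post-treatment visit would be the baseline score. These are fair hints that pre-treatment may have been meant as a time level, but they do not override a list of terms that names the time levels and the covariates. If they are right, the parenthesis needs correcting.

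The second reply is that nothing is invalid, and this stands in full. A reader might infer that omitting baseline biases the estimate, inflates the type I error or leaves the trial underpowered. The documents support none of these: randomisation protects the first two, and the 64 per group was computed without adjustment.

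A reader might also infer that the treatment effect will be judged by the group-by-time interaction, which with post-treatment levels alone would test only whether the effect changes over follow-up. The plan does not say so; it says that group differences will be calculated from the model.

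Finally, the gain depends on an assumed correlation, is smallest at the low end (80% to 84%), and matters less for pain than for disability. That stands too, and it limits the size of the point.

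**Conclusion.** The point holds as a matter of efficiency and clarity. On the stated terms, baseline NPRS and CF-PDI enter the model neither as a time level nor as covariates, though both are collected. The forgone gain for CF-PDI is a variance reduction of up to 9%, 25% or 49% at correlations of 0.3, 0.5 or 0.7, which corresponds to power of at most about 84%, 90% or 98% in place of 80%. For NPRS it is mainly a narrower interval. These sizes rest on the assumed correlations, the protocol's SDs, 64 analysed per arm, a single visit, and a comparator without covariates; the covariates already planned would make the gain smaller. The change is worth making because it uses data in hand, not because the present plan fails.

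**What to change.** - Add the participant's baseline value of the analysed outcome as a covariate, with its interaction with time: baseline NPRS in the NPRS model, CF-PDI in the CF-PDI model, and PSEQ in the PSEQ model.
- For TSK/TMD, confirm that the psychosocial covariate is the baseline score. If it is, nothing needs adding for that outcome.
- State that the treatment effect is the model's group contrast at each post-treatment visit.
- If pre-treatment was meant as a time level, correct the parenthesis and constrain the baseline means to be equal between the groups. A plain change score should not be used in place of this.
- Leave GPE out of the change unless its pre-treatment score is confirmed to be usable. It is listed at the initial assessment and its question refers back to the start of the episode, but it is a rating of perceived change.

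The cost is a sentence or two in the analysis plan and a few model parameters. No new data and no change in sample size are needed. The change should be recorded before allocation is unblinded.

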### Analysis of the population

In the event of two consecutive absences from treatment sessions, patients will be contacted by telephone. The analysis will follow the intention-to-treat principles. An intention-to-treat analysis will be performed using the patient’s most recent assessment in case of withdrawals or absence of data. Possible adverse effects (injuries) occurring during the intervention period, the individuals will be referred for appropriate treatment.

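### Last observation carried forward is fixed as the intention-to-treat rule for a mixed model that does not need it; it biases the group difference by an amount set by the timing and balance of dropout

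*Protocol article*

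**What the plan says.** Two sections of the protocol article fix the rule. Data analysis says of missing scores: "we will replace the value by the last observation carried forward". Analysis of the population: "An intention-to-treat analysis will be performed using the patient’s most recent assessment in case of withdrawals or absence of data". Neither limits it by outcome, visit or reason, and neither calls it a sensitivity analysis. The only further analysis named for incomplete participants is a per-protocol one that drops those who did not finish the six weeks.

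The model is also fixed. Effects "for all outcomes (primary and secondary) will be calculated using linear mixed models". Its terms are group, time and their interaction, plus covariates. The text below Table 1 says that a blinded researcher "will run the assessments pre-treatment, immediately after and at 1-month and 3-month follow-ups", so there is one baseline score and three later ones. Sample size calculation expects some loss: "considering a follow-up loss up to 15%, we will recruit 148 participants".

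**The concern.** Last observation carried forward (LOCF) assumes that a participant's score would have stayed where it was last seen. That is hard to defend here. Both arms receive six weeks of manual therapy and exercise, which the Background describes as effective for pain and disability. A participant lost before the post-treatment assessment has only a baseline score, and under this rule that untreated score becomes the result at all three later visits.

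A linear mixed model fitted by likelihood does not need the gaps filled. If correctly specified, it gives valid estimates from incomplete repeated outcomes under missing-at-random. Filling the gaps first gives up that property and enters copied scores as if they had been measured. The order of the two steps is not written out, but no other reading is natural. At stake is the estimate for both primary outcomes in the main analysis.

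**Working it through.** **The plan's own figure.** For disability, f = 0.25 (d = 0.50) with 80% power and two-sided alpha 5% (sidedness assumed) gives 64 per group, as stated. 128 × 1.15 = 147.2, taken up to 148, or 74 per arm. The figures reproduce and none needs to change. With 15% loss, 74 × 0.85 = 62.9, so about 63 per arm are observed.

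**Inputs.** From Sample size calculation: CF-PDI difference 5.08, SD 10, loss up to 15%. Assumed, because the documents do not give them: a 10-point improvement in both arms (so 15.08 with PNE if the effect is real), SD 10 at every visit, loss at random, and its timing. The within-person correlation of 0.5 matters only when the analysis adjusts for baseline.

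**Formula.** If a share p of an arm carries its baseline score and the true improvement is δ, LOCF has expected improvement (1 − p)δ and variance 100 + p(1 − p)δ². Two timings bracket the case:
- Early: all loss precedes the post-treatment visit, so p is the full loss. This is unfavourable to LOCF.
- Spread: loss is even over the three visits and improvement is complete at post-treatment and then stable, so for the 3-month contrast only a third of the loss carries baseline. This is favourable to LOCF.

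**Equal loss, 15% per arm, true difference 5.08** (critical value 1.976)
- Early: 0.85 × 5.08 = 4.32. SE = √[(129.0 + 112.75)/74] = 1.81. Power = Φ(4.32/1.81 − 1.976), about 66%.
- Spread: 0.95 × 5.08 = 4.83. SE = √[(110.8 + 104.75)/74] = 1.71. Power about 80%.
- Observed data only, 63 per arm, unadjusted: 5.08 without bias, power about 81%.

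**Unequal loss, 20% against 10%, no true effect**
- Early: bias = (0.20 − 0.10) × 10 = 1.0 point. SE = √[(116 + 109)/74] = 1.74. Type I error about 8.6%; simulations gave 8% to 9.5%.
- Spread: bias = (0.067 − 0.033) × 10 = 0.33 point. SE = √[(106.2 + 103.2)/74] = 1.68. Type I error about 5.3%; simulation gave about 5.6%.

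**Unequal loss, true difference 5.08**
- Early, PNE arm loses 20%: 0.80 × 15.08 − 0.90 × 10 = 3.06. Control loses 20%: 0.90 × 15.08 − 0.80 × 10 = 5.57.
- Spread: 0.933 × 15.08 − 0.967 × 10 = 4.4, and 0.967 × 15.08 − 0.933 × 10 = 5.2.

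**Baseline adjustment.** With early loss, simulated power at 15% per arm is about 78%, against 90% from observed data. Type I error at 20% against 10% is about 11%. Adjustment does not remove the bias.

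**A second check, on pain.** Assumed NPRS means at baseline and the three later visits: control 6.7, 5.0, 4.7, 4.5; PNE 6.7, 4.0, 3.2, 2.5 (true 3-month difference −2). SD 3 is from the plan; loss is spread evenly.
- 15% loss per arm: 0.85 × (−2) + 0.05 × (0 − 1.0 − 1.5) = −1.825, an attenuation of about 9%.
- Loss of 5% in control and 25% in PNE: −1.52. Reversed: −2.13.
- If loss depends on the previous pain score (simulated): −1.79 with equal loss, −1.22 and −2.37 with unequal loss. With no true effect, the unequal cases give a bias of about 0.45 point and type I error of about 17%; equal loss keeps it near 5%.
- A missing-at-random estimate from the observed data gave about −2.00 in every scenario.

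**Standard error.** In the pain runs with 15% random loss per arm, the LOCF model SE was 0.43 to 0.44, in line with LOCF's own sampling spread (0.42 to 0.43). It was about 4% to 6% below the spread of the observed-data estimate (about 0.46).

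**The case against.** The best defence is that the harm may be small. The plan gives 15% as an upper limit and says nothing about timing. If loss is spread over the visits and patients have stopped changing by the end of treatment, the attenuation is about 5% and power is essentially that of an observed-data analysis. With equal loss, type I error is kept and the bias runs towards no effect, which is conservative for a superiority hypothesis. All of this stands, and it is why the size is given as a range.

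Four stronger readings are tempting, and the documents do not support them.
- A reader might take 4.3 points, 66% power and 9% type I error as the expected result. They arise only if all loss precedes the post-treatment visit.
- A reader might infer that the standard error is seriously wrong. The LOCF model SE matched its own sampling spread, and the apparent gain over an observed-data analysis is only a few per cent.
- A reader might expect unequal dropout because one arm has an extra component. PNE is confined to the first two sessions, the other arm is offered compensating attention, and both follow the same assessments. Imbalance is possible but not predicted.
- A reader might assume that everyone who stops treatment has only a baseline score. Nothing says that such participants are not assessed, and absentees are telephoned after two missed sessions.

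What the defence does not rescue is the rule itself. LOCF is not reliably conservative: with more loss in the control arm it can exaggerate the effect, and the direction cannot be known in advance.

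**Conclusion.** The point holds. The article fixes LOCF as the primary intention-to-treat rule for both primary outcomes, so this is not a detail left to an unseen analysis plan. It adds an implausible no-change assumption to a model that works without one.

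Under the CF-PDI assumptions, the loss of estimated effect at 15% per arm is between about 0.25 point (5.08 − 4.83) and 0.76 point (5.08 − 4.32). With 20% against 10% loss and no true effect, the bias is about 0.3 to 1.0 point and type I error about 5.5% to 9%, unadjusted. A smaller true improvement shrinks the unequal-loss bias in proportion: with 5 points instead of 10, the early-loss bias is 0.5 point and type I error about 6%. Loss that depends on pain and differs between arms can do more, as the pain check shows. The main harm is bias; any false gain in precision is small.

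**What to change.** In both Analysis of the population and Data analysis, delete LOCF as the primary rule. State instead that the linear mixed model is fitted by REML to all observed NPRS and CF-PDI assessments of every randomised participant, in the assigned arm, under missing-at-random.

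Enter the baseline score as a repeated response with a mean common to both arms. Fitting post-baseline visits alone would not be enough: participants with only a baseline score would contribute nothing, and loss related to baseline severity would not be handled.

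Use baseline values for the psychosocial and NPQ covariates, because a mixed model tolerates missing outcomes but not missing covariates. Add a delta-adjusted sensitivity analysis for departures from missing-at-random, and keep LOCF at most as a labelled sensitivity analysis.

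The cost is revised wording in two sections and slightly more analysis work. No extra participants, visits or data are needed, and the planned SPSS software can fit the model to incomplete repeated measures. The change should be made before unblinding.
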